# Revision History

| Revision | Date              | Author(s) | Description                                                                                                                                                                                                                                                                                                                                                     |
|----------|-------------------|-----------|-----------------------------------------------------------------------------------------------------------------------------------------------------------------------------------------------------------------------------------------------------------------------------------------------------------------------------------------------------------------|
| 1.0      | 11th October 2017 | ✖         | Created                                                                                                                                                                                                                                                                                                                                                         |
| 1.1      | 17th October 2017 | ✖         | Fixes on Å§3.3. Defined end of follow-up period and some clinical variables.                                                                                                                                                                                                                                                                                    |
| 1.2      | 11th January 2018 | ✖         | Changed biobank handling in sampling protocol.                                                                                                                                                                                                                                                                                                                  |
| 1.3      | 2nd February 2018 | ✖         | Changed blood tube in sampling protocol.                                                                                                                                                                                                                                                                                                                        |
| 2.0      | 3rd March 2020    | ✖         | Added new control arm. Elaborated eligibility criteria for controls. Removed exclusion criteria (prior history of cancer, history of radiation) and one inclusion criterion (available cytology results) for cases. Removed comparisons (all secondary endpoints) with cytology given its role in control eligibility criteria. Remove non-BCa subset analysis. |

## Introduction

The present document describes the protocol for a study to verify whether laboratory measurements of glycosaminoglycans (GAG) in plasma and/or urine samples can accurately distinguish bladder cancer (BCa) positive versus control subjects.

The present document contains the following items:

1. Study rationale;
2. Study design;
3. Protocols.

## Chapter 2

# Study rationale

This study aims at characterizing a novel class of circulating cancer biomarkers, namely glycosaminoglycans (GAG), in bladder cancer (BCa). Published evidence demonstrated the elevated diagnostic potential of circulating GAGs in clear cell renal cell carcinoma (ccRCC) with accuracy of detection versus healthy individuals ranging 92.7% to 100% depending whether only urine, only plasma, or both fluid combined were used. Preliminary results indicated a similar level of accuracy in prostate cancer (PCa). In this chapter, we will briefly describe the need of circulating biomarkers in cancer and BCa; the published and preliminary evidence of GAG as potential diagnostic biomarkers; the purpose of this study.

### 2.1 Circulating biomarkers in BCa

The current diagnostic workup of many cancers would largely benefit from simpler noninvasive or minimally invasive diagnostic procedures, for example a blood or urine test. Despite intense research, very few diagnostic tests based on blood or urine biomarkers entered clinical practice.

In BCa, early diagnosis is generally considered to produce a better outcome in patients. Contrary to muscle-invasive BCa (MIBC) or high-grade non-muscle invasive BCa (NMBIC), which tend to progress to MBIC, low-grade BCa is associated with generally good prognosis. In the asymptomatic population, the incidence of BCa is too low to warrant screening with current technologies (Roobol, M.J., et al. Feasibility study of screening for bladder cancer with urinary molecular markers (the BLU-P project). *Urol Oncol*, 2010. 28: 686.; Lotan, Y., et al. Should we screen for bladder cancer in a high-risk population?: A cost per life-year saved analysis. *Cancer*, 2006. 107: 982). In patients with hematuria, current urinary markers are not specific enough to replace cystoscopy, while urine cytology is not sensitive enough for low-grade BCa. Therefore, cystoscopy is the gold standard for primary diagnosis. The introduction of sensitive urinary biomarkers may reduce the need of unnecessary cystoscopy in symptomatic patients.

## 2.2 Glycosaminoglycans as circulating cancer biomarkers

One of the problems affecting the discovery of cancer-specific biomarkers in accessible fluids is the complex nature of cancer itself. Cancer heterogeneity remains a paramount challenge to develop effective biomarkers, in that future cancer biomarkers are required to be broad enough to capture the complexity of the cancer (sensitivity) - while narrow enough to exclude confounding diseases. A single molecule, e.g. a given protein, appears to have very limited biological potential to fulfill both requirements. A different way to tackle the problem of cancer heterogeneity is to rationalize a selected panel of biomarkers, broad enough to effectively speak for cancer while narrow enough to make its measurement amenable. We refer to such panels as systems biomarkers. A rational approach to discover systems biomarkers was put forward in the field of systems biology.

In a 2016 study, we utilized a systems biology approach to map omics data from clear cell renal cell carcinoma (ccRCC), the most common form of kidney cancer, onto an exhaustive reconstruction of the human metabolic network. The bioinformatics analysis eventually narrowed down the search to the pathway that leads to the synthesis and modification of GAGs, in particular on chondroitin and heparan sulfate. Virtually every step in this pathway was deregulated in ccRCC and exacerbated in metastasis. The candidate systems biomarker was therefore defined as the set of all possible modifications of these GAGs, a total of 18 independent GAG properties. A multicenter study was undertaken at Veneto Institute of Oncology in Padua, Italy and Sahlgrenska University Hospital in Gothenburg, Sweden to form a discovery cohort of retrospective and prospective samples from 50 healthy subjects and patients with metastatic ccRCC. GAGs were then measured in plasma and urine. The systems biomarker showed dramatic differences metastatic ccRCC versus healthy samples. We designed GAG scores to condense all the measurements that make up the systems biomarker. These GAG scores displayed an excellent ability to detect metastatic ccRCC with accuracies ranging 93.1% in the urine to 100% in the plasma. These figures were confirmed in an independent validation cohort comprising 33 new subjects, further demonstrating that the GAG scores normalize in patients with former diagnosis of ccRCC but no evidence of disease (NED). Results are collectively shown in Figure 2.1.

We have recently generated preliminary results that indicate that this systems biomarker could apply to PCa. Twenty-nine samples from patients with PCa collected at Prostate Cancer Center at the University of British Columbia in Vancouver, Canada were compared to 26 healthy individuals previously sampled. Samples were equally split into a discovery and validation cohort. We designed a blood and urine score that achieved exceptional accuracy in the discovery cohort. The validation of these scores in the validation cohort confirmed extremely elevated AUC, ranging 0.923 in the urine, 0.956 in the blood, and 0.995 when combined (Figure 2.2). Remarkably, the combined PCa score is specific to PCa as opposed to ccRCC (Figure 2.3). This indicates that GAGs acquire a specific signature in association with PCa, markedly distinct from

[figure not shown]

Figure 2.1: Plasma and urine score based on GAG profiling (left) and corresponding ROC curves (right) in healthy vs. metastatic clear cell renal cell carcinoma (mccRCC) vs. no evidence of disease (NED) subjects. Adapted from Gatto et al. (2016).

healthy individuals, and sufficiently different from ccRCC subjects.

[figure not shown]

Figure 2.2: Plasma and urine score based on GAG profiling in the discovery (A) and validation (B) cohort of PCa vs. healthy samples. The ROC curves (C) refer to the validation cohort and the sensitivity/specificity at the optimal cutpoint found in the discovery cohort are displayed.

The results of these studies are suggestive that GAGs might be useful diagnostic biomarkers in urological malignancies. In this study, we will therefore evaluate the potential of GAG biomarkers in BCa.

# Study design

The design of this study is articulated as a case-control study for phase 1, wherein continued enrollment in the case arm can constitute a cohort study for phase 2. A diagram of the study is shown in Figure [3.1](#)

[figure not shown]

Figure 3.1: Study design. The study population is a consecutive series of patients referred to transurethral resection of the bladder (TURB) for BCa. In phase 1, a case-control study is formed by including healthy subjects as controls from a historical cohort and patients with no evidence of disease after TURB for BCa as clinical controls.

Table 3.1: Eligibility criteria in the case arm.

| Inclusion criteria                                                        | Exclusion criteria                          |
|---------------------------------------------------------------------------|---------------------------------------------|
| Referred to transurethral resection of the bladder (TURB) for primary BCa | No histopathological diagnosis of BCa Ta-T4 |
| Signed informed consent                                                   | N0-2 MX-0 after TURB                        |
| Fit to undergo all protocol procedures                                    | History of bladder or prostate radiation    |

Table 3.2: Eligibility criteria in the control arm for healthy volunteers.

| Inclusion criteria                                                                             | Exclusion criteria              |
|------------------------------------------------------------------------------------------------|---------------------------------|
| > 18 years of age                                                                              | Age- and sex-unmatched to cases |
| No diagnosis of cancer at the baseline visit or within 18 months after the baseline visit      |                                 |
| Available glycosaminoglycans' measurements analysed in the same way as the prospective samples |                                 |
| Signed informed consent                                                                        |                                 |

### 3.1 Study population

The study population is a consecutive series of patients referred to transurethral resection of the bladder (TURB) for BCa.

### 3.2 Eligibility criteria

For cases, the criteria were designed to obtain maximize a real-world distribution of significant BCa diagnoses as assessed by cystoscopy. The selection is biased towards higher grade BCa due to exclusion of cystoscopic findings treated by coagulation. The criteria are described in Table 3.1.

For controls, the criteria were different from historical healthy volunteers (Table 3.2) and patients with no evidence of disease (Table 3.3).

### 3.3 Study data collection

Each patient enrolled in this study will have two pieces of data collected - biological samples and clinical metadata. Biological samples collected for this study are described in Table 3.4. Clinical metadata collected for this study are

Table 3.3: Eligibility criteria in the control arm for patients with no evidence of disease.

| Inclusion criteria                                                                                                                                                                          | Exclusion criteria                                                                 |
|---------------------------------------------------------------------------------------------------------------------------------------------------------------------------------------------|------------------------------------------------------------------------------------|
| In follow-up with cystoscopy after treatment Ta-T3 N0-2 M0 BCa or upper tract urothelial cancer and no evidence of disease at cystoscopy for at least 6 months prior to the inclusion visit | Positive cytology at the inclusion visit                                           |
| No history of cancer except urothelial                                                                                                                                                      | Any intravesical instillation therapy during 6 months prior to the inclusion visit |
| Signed informed consent                                                                                                                                                                     |                                                                                    |

Table 3.4: Biological samples collected for each patient.

| Sample type | Description                                                                                                               |
|-------------|---------------------------------------------------------------------------------------------------------------------------|
| Plasma      | 12 x 220 uL of plasma from 1 blood draw is collected according to protocol in Chapter 4. It is collected pre-operatively. |
| Urine       | 12 x 220 uL of urine from 1 urine draw is collected according to protocol in Chapter 4. It is collected pre-operatively.  |

Table 3.5: Clinical metadata collected for each patient.

| Variable                                      | Description                                                          |
|-----------------------------------------------|----------------------------------------------------------------------|
| Year of Birth                                 | YYYY format                                                          |
| Family history of cancer                      | Yes/No and Relative (Father/Brother).                                |
| History of cancer                             | Yes/No and Histological Type                                         |
| History of confounding morbidities            | Yes/No for Urinary tract infection/Prostatitis/Prostate hyperplasia  |
| Date of TURB                                  | DD.MM.YYYY                                                           |
| Definitive diagnosis after TURB               | BCa/Others                                                           |
| Urine cytology assessment of cancerous cells  | Positive/Negative                                                    |
| Date of urine cytology                        | DD.MM.YYYY                                                           |
| Date of sampling                              | DD.MM.YYYY                                                           |
| Pathologic tumor grade                        | Tumor grade evaluated by pathologic diagnosis                        |
| Pathologic TNM stage                          | Tumor TNM stage evaluated by pathologic diagnosis                    |
| Number of tumors                              | Integer                                                              |
| Tumor diameter                                | In cm                                                                |
| Concurrent carcinoma in situ                  | Yes/No                                                               |
| Date of last known alive                      | DD.MM.YYYY as either last follow-up visit or per population registry |
| Status when last known alive                  | No evidence of disease/Localized/Locally-advanced/Metastatic/Unknown |
| Date of death                                 | DD.MM.YYYY                                                           |
| Cause of death                                | BCa/Other/Unknown                                                    |
| Date of recurrence                            | DD.MM.YYYY as evaluated by cystoscopy                                |
| Date of progression                           | DD.MM.YYYY as evaluated by cystoscopy                                |
| Date of first cycle of intravesical treatment | DD.MM.YYYY                                                           |
| Type of intravesical treatment                | Bacillus Calmette-Guerin/Mitomycin                                   |

described in Table 3.5. Follow-up data for a given patient will be collected up to 6 months after date of registration.

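### NED controls need no cystoscopy at inclusion and no recent one on record, so a few could carry an undetected recurrence when sampled

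*Supplement*

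**What the plan says.** All references are to revision 2.0 of the protocol.

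- **Who the NED controls are.** Table 3.3 (section 3.3) takes patients "In follow-up with cystoscopy after treatment Ta-T3 N0-2 M0 BCa or upper tract urothelial cancer", with "no evidence of disease at cystoscopy for at least 6 months prior to the inclusion visit".
- **What is tested at the visit.** The same table excludes on "Positive cytology at the inclusion visit". No other test is tied to the inclusion visit.
- **How the protocol rates the two tests.** Section 2.1 states that "urine cytology is not sensitive enough for low-grade BCa" and that "cystoscopy is the gold standard for primary diagnosis".
- **When samples are taken.** For both fluids Table 3.4 says only "It is collected pre-operatively", which does not describe a control who is not having an operation.
- **What is recorded.** Table 3.5 lists the dates of sampling, of cytology and of any recurrence ("DD.MM.YYYY as evaluated by cystoscopy"). It has no field for the date or result of the cystoscopy that made the control eligible. Section 3.3 collects follow-up to 6 months after registration.
- **The other control group.** Table 3.2 asks of healthy volunteers "No diagnosis of cancer at the baseline visit or within 18 months after the baseline visit". Table 3.3 has no counterpart.
- **Where NED controls enter.** The caption of Figure 3.1 makes them the clinical controls of phase 1, section 2.3 sets BCa against control samples, and section 3.5 promises a 2x2 table for every case-control comparison. Section 3.4.1 defines the primary endpoint, with its low-grade subset, against healthy controls.

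**The concern.** A NED control's label has to be true when the GAG sample is taken. Everyone in this group has had urothelial cancer, so recurrence is the obvious way for the label to be wrong. As written, the stronger examination may lie at an unspecified distance before the sample, while the test done at the visit is the one the protocol considers weak for low-grade tumour.

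A control with an unseen recurrence and a positive score would be counted as a false positive. The score would then look less specific against its clinical controls than it is. Because the cystoscopy date is not among the listed data, an analyst could not later check how far the reference examination and the sample were apart.

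**Working it through.** The plan states no figure on this point, so there is none to reproduce. The check has two parts.

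**1. The wording**

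The cystoscopy criterion can be read in two ways.

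- *Disease-free status sustained over a period that runs up to the visit.* This may imply some examination inside that period, but it does not say when, and it does not require one at the visit.
- *A clear cystoscopy some time before the visit.* This gives a minimum look-back and no maximum.

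Neither reading requires a cystoscopy at the visit or states a limit on the age of the last one. An undetected tumour at sampling is possible under both.

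The items that might close the gap do not. Table 3.5 would capture a recurrence found within 6 months, but no rule excludes or reclassifies a control on that basis.

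**2. Possible size (illustration on assumed inputs)**

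The documents give no recurrence prevalence, no accuracy figures for cytology and no expected AUC in BCa. All inputs below are assumptions.

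*How much cytology removes.* Let p be the tumour prevalence among candidate controls at sampling, and Se and Sp the sensitivity and specificity of cytology. The share of enrolled controls with tumour is

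r = p(1 − Se) / [p(1 − Se) + (1 − p)Sp].

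Example with p = 10%, Se = 10%, Sp = 95%: 0.09 / (0.09 + 0.855) = 9.5%. With Se = 40%: 0.06 / (0.06 + 0.855) = 6.6%.

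*Effect on the AUC.* The AUC is the probability that a case outscores a control, so it is linear in the mix of controls. If missed tumours score like cases,

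observed AUC = (1 − r) × true AUC + r × 0.5.

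| p before cytology | r after cytology (Se 40% to 10%, Sp 95%) | Observed AUC if true AUC is 0.80 |
|---|---|---|
| 2% | 1.3% to 1.9% | 0.796 to 0.794 |
| 5% | 3.2% to 4.8% | 0.790 to 0.786 |
| 10% | 6.6% to 9.5% | 0.780 to 0.771 |
| 20% | 13.6% to 19.2% | 0.759 to 0.743 |

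Setting r directly:

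- r = 5%: 0.95 × 0.80 + 0.05 × 0.5 = 0.785
- r = 10%: 0.90 × 0.80 + 0.10 × 0.5 = 0.770
- r = 15%: 0.85 × 0.80 + 0.15 × 0.5 = 0.755

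If a case outscores a missed tumour with a probability halfway between 0.5 and 0.80, that is 0.65, the loss halves. At r = 10%: 0.90 × 0.80 + 0.10 × 0.65 = 0.785.

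*Effect on specificity.* Observed specificity = (1 − r) × true specificity + r × (1 − sensitivity). With an assumed true specificity of 0.90 and sensitivity of 0.70 for the GAG score, r = 10% gives 0.90 × 0.90 + 0.10 × 0.30 = 0.84.

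*Set against sampling error.* The Hanley-McNeil standard error at AUC 0.80 with 20 cases (section 3.6.4 aims for at least 20 G1 tumours) is 0.071 with 20 controls and 0.062 with 100 controls (control numbers assumed). The shifts of 0.015 to 0.045 for r of 5% to 15% are all below one standard error.

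**The case against.** Much of the opposing case stands.

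- **The named analyses do not use these controls.** A reader might infer that the primary AUC, or the pre-specified low-grade subset, is diluted. Section 3.4.1 sets both against healthy controls, who enter under Table 3.2, so the wording of Table 3.3 does not reach them.
- **One reading should not be taken as fact.** A reader might infer that a patient on yearly surveillance, last examined 10 months earlier, plainly qualifies. The documents give no surveillance interval, and on the sustained-status reading that patient arguably does not qualify.
- **Sampling at the inclusion visit is inferred.** The only stated timing is pre-operative. The visit may in practice coincide with a surveillance cystoscopy, and Figure 3.1 is not shown. If it does coincide, the amendment only writes down existing practice.
- **Section 2.1 is narrower than it may seem.** It discusses patients with hematuria, says cytology is insufficiently sensitive rather than blind, and calls cystoscopy the gold standard for primary diagnosis, not for surveillance.
- **Some missed tumours would surface.** Recurrence by cystoscopy is recorded over 6 months and could support a sensitivity analysis, although none is planned.
- **The illustration is at the upper end.** Cases are referred to TURB for primary BCa, and section 3.2 says findings treated by coagulation are excluded. A small unseen recurrence may well score lower than such cases.

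None of this supplies what is missing: a cystoscopy tied to the sample, a limit on its age, or a record of its date.

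**Conclusion.** The gap is real but limited. Table 3.3 allows a NED control to be enrolled with an undetected recurrence, and Table 3.5 does not let an analyst find out how recent the clearing cystoscopy was. The consequence falls on phase 1 comparisons with the NED clinical controls, where apparent AUC and specificity would be lowered. The primary endpoint and low-grade subset as worded are untouched.

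The size cannot be known from the documents. An AUC of 0.785 to 0.755 in place of 0.80 rests on three assumptions: the true AUC, 5% to 15% of controls affected, and missed tumours scoring like cases. At 2% prevalence the loss is under 0.01. If missed tumours score higher than clear controls, the bias is conservative: it understates the score's performance and cannot by itself produce a falsely favourable result. The change is worth making because it is cheap and removes a doubt that cannot be resolved afterwards from the listed data.

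**What to change.** 1. Amend Table 3.3 so that NED controls are included and sampled at an already scheduled follow-up cystoscopy that shows no evidence of disease, keeping the existing disease-free period of at least 6 months.
2. State that anyone whose cystoscopy at that visit is positive is not counted as a control.
3. Add the date and result of that cystoscopy to Table 3.5.

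These are rules for study eligibility and sample timing. They add no procedure and leave surveillance as it is, since these patients are already in cystoscopic follow-up. The cost is some rewording, two data fields, sampling that must fit the existing appointment, and the possible loss of a few candidate controls.

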## 3.4 Study endpoints

### 3.4.1 Primary endpoint

The primary endpoint of the study is the AUC of GAG-scores in BCa vs. healthy controls. AUC is the area-under-the-receiver-operating-curve and GAG-scores are derived from a scoring system that uses measurements of GAGs in plasma and/or urine samples.

The following pre-specified subset analyses will be carried out:

1. Alternative case definitions:

- (a) Cases are defined as low-grade BCa;

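### Other cancers are kept out of the healthy controls but not out of the bladder cancer cases, which may bias the primary AUC upward by an unknown amount

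*Supplement*

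**What the plan says.** All references are to protocol v2.0 in the Supplement.

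- **Cases (Study design, Table 3.1).** Entry is by "Referred to transurethral resection of the bladder (TURB) for primary BCa", with histopathological confirmation of bladder cancer after TURB. The only criterion touching another cancer is the exclusion "History of bladder or prostate radiation". The revision history records for v2.0: "Removed exclusion criteria (prior history of cancer, history of radiation". Table 3.1 still prints the radiation exclusion, so I treat it as in force.
- **Healthy controls (Study design, Table 3.2).** "No diagnosis of cancer at the baseline visit or within 18 months after the baseline visit". They are also age- and sex-matched to the cases.
- **Controls with no evidence of disease (section 3.3, Table 3.3).** "No history of cancer except urothelial".
- **Primary endpoint (section 3.4.1).** "The primary endpoint of the study is the AUC of GAG-scores in BCa vs. healthy controls". The score is said to come from a scoring system using plasma and/or urine GAGs; how it is built is not described. The one subset analysis shown takes low-grade disease as the case definition.
- **Data collected (section 3.3, Table 3.5).** History of cancer is recorded as "Yes/No and Histological Type". Follow-up runs to 6 months after registration.
- **Rationale (section 2.2).** In prostate cancer, the validation cohort "confirmed extremely elevated AUC, ranging 0.923 in the urine, 0.956 in the blood, and 0.995 when combined". In metastatic clear cell renal cell carcinoma (ccRCC), accuracy was 93.1% in urine and 100% in plasma.

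**The concern.** Eligibility differs between the two arms of the primary comparison on a factor that, by the protocol's own account, can alter the marker. A healthy control diagnosed with any cancer at baseline, or in the following 18 months, is removed. A bladder cancer case with a concurrent kidney cancer, or a prostate cancer that was not irradiated, stays in. Matching on age and sex does not restore the balance, because the cancers expected at that age are taken out of one arm only.

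If the bladder cancer score responds to those cancers, part of the AUC reflects them and not the bladder tumour. If the score is derived on these same samples, it may also give weight to that signal. At stake is how far the primary AUC can be read as evidence of a bladder cancer signal. Unlike sampling error, such a bias does not shrink as more patients are enrolled.

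**Working it through.** **The plan's own figures.** The protocol gives no share of cases with another cancer and no expected AUC, so there is no figure on this point to reproduce. The only planning number is a minimum of 20 cases (section 3.6.4). It comes without alpha, power, AUC or number of controls, and it is not in dispute here.

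**Formula.** For a fixed score, the AUC over a mixed case group is the weighted mean of the component AUCs:

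AUC_obs = (1 − q) × AUC_b + q × AUC_o, so shift = q × (AUC_o − AUC_b).

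**Inputs.**
- q, the share of cases with another cancer active at sampling: not in the documents. Assumed 5%, 10% and 20%.
- AUC_b, the AUC in cases with bladder cancer only: not in the documents. Assumed 0.70, 0.80 and 0.90.
- AUC_o, the AUC in cases with bladder cancer plus another cancer: not in the documents. Assumed equal to the prostate cancer values in section 2.2, from 0.923 (urine) to 0.995 (combined). Those belong to a score built for prostate cancer, so carrying them over is itself an assumption.

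**Example.** With q = 10% and AUC_b = 0.70: 0.90 × 0.70 + 0.10 × 0.923 = 0.722, and 0.90 × 0.70 + 0.10 × 0.995 = 0.730 (rounded from 0.7295).

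**Upward shift for AUC_o from 0.923 to 0.995:**

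| AUC_b | q = 5% | q = 10% | q = 20% |
|---|---|---|---|
| 0.70 | 0.011 to 0.015 | 0.022 to 0.030 | 0.045 to 0.059 |
| 0.80 | 0.006 to 0.010 | 0.012 to 0.020 | 0.025 to 0.039 |
| 0.90 | 0.001 to 0.005 | 0.002 to 0.010 | 0.005 to 0.019 |

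**Other directions.** If the second cancer adds nothing, AUC_o = AUC_b and the shift is 0. If it pulls the profile away from the bladder cancer pattern, the shift is negative: with AUC_b = 0.70, AUC_o = 0.50 and q = 10%, it is 0.10 × (0.50 − 0.70) = −0.02.

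**Scale.** With 20 cases and an assumed 26 to 50 controls, the Hanley-McNeil 95% half-width is 0.156 to 0.144 at an AUC of 0.70, 0.134 to 0.126 at 0.80, and 0.098 to 0.095 at 0.90. The shifts above are well inside that.

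**Limit of the calculation.** It holds the score fixed. If the score is fitted to these samples, the composition of the case group can also change the score, which the formula does not capture.

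**The case against.** The strongest reply is that the rationale also contains evidence against a bias. Section 2.2 reports that scores normalise in former ccRCC patients with no evidence of disease, so a treated past cancer may add nothing. It also reports that the combined prostate cancer score separates prostate cancer from ccRCC, so a score for one cancer need not respond to another. A reader might infer from the eligibility tables that the AUC is inflated; given these statements, the documents do not establish that. They do not remove the risk either. The first covers one treated cancer, while Table 3.1 also admits active ones. The second describes a prostate cancer score and does not show how a bladder cancer score behaves. Both come from small cohorts.

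Three further points stand against stronger readings:

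- A reader might infer that other cancers are being counted as bladder cancer. They are not: every case needs histological confirmation, so the issue is a past or co-existing cancer in a bladder cancer patient.
- A reader might infer that the rule in Table 3.3 affects the primary AUC. It does not, because section 3.4.1 compares cases with healthy controls. The rule that matters is in Table 3.2, and it does not expressly bar a remote cancer history.
- A reader might treat the ccRCC figures as AUCs for kidney cancer in general. They are accuracies, and in metastatic disease.

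It is also fair to say that the case arm was opened deliberately, that section 3.2 aims at a real-world distribution of diagnoses, and that phase 1 is an early step before cohort studies. That supports keeping enrolment open. It does not argue against looking at the effect. Finally, no separate analysis plan is among the documents, so a restricted analysis may be planned elsewhere; the eligibility difference itself is in the protocol.

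**Conclusion.** The asymmetry is real in the current version, and it lies on a factor that the protocol links to the marker. An upward bias in the primary AUC is possible but not shown. Its size is unknown: about 0.02 to 0.03 at a bladder cancer AUC of 0.70 and at most 0.01 at 0.90, if 10% of cases have an active second cancer detected as well as prostate cancer was in section 2.2. It is zero if the second cancer adds no signal, and it could be negative. Both the share and the second-cancer AUC are assumptions.

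A reader might go further and ask that cases with another cancer be dropped from the primary analysis. The documents do not support that: the field in Table 3.5 shows neither date nor disease status, so dropping on it would also remove treated cancers that section 2.2 suggests may be harmless. An added pre-specified analysis is the proportionate response. This is a cheap improvement worth making, not a flaw that invalidates the design.

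**What to change.** - **Section 3.4.1.** Keep the AUC in all cases. Beside it, pre-specify the AUC, and any derivation of the score, restricted to cases with no non-urothelial cancer in the history-of-cancer field of Table 3.5. State that a claim of a bladder cancer signal rests on the two agreeing.
- **Table 3.5.** Add to that field the date of the other cancer and whether it was active at sampling, so that treated and active disease can be told apart.
- **Reporting.** Give the number of cases with another cancer by histology. Note that the restricted set will not mirror Table 3.2 exactly, because controls have an 18-month look-forward and cases 6 months of follow-up.

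**Cost.** One or two sentences in section 3.4.1 and two extra items per affected patient; enrolment does not change. The restricted analysis has fewer cases and a wider interval. With numbers near the 20-case minimum, agreement between the two AUCs should be judged on the estimates and their intervals, not on whether each is statistically significant.
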